## Methods

### Aims

The primary objective is to determine the efficacy of CBM training, compared to sham training, in a population undergoing inpatient withdrawal treatment from alcohol, in terms of their abstinence rates at 2 weeks post-discharge.

The secondary objectives are:To determine the efficacy of CBM training compared with sham training, in a population undergoing inpatient withdrawal treatment for AUD, in terms of their abstinence rates at 3, 6, and 12 months post-discharge.To determine whether the efficacy of CBM compared to sham training is moderated by the strength of approach bias at baseline.To determine whether the efficacy of CBM is moderated by risk-taking impulsivity.To determine whether participants who undergo CBM training will demonstrate a reduction in self-reported cue-evoked desire (wanting) for alcohol compared to those who undergo sham training.To determine whether those who receive CBM training impose a lower burden on healthcare services in terms of reduced use of emergency healthcare services and readmission to alcohol and other drug (AOD) withdrawal treatment services in the year following discharge, relative to those who receive sham training. These data will be used to estimate the cost savings to the healthcare system that would be associated with introducing CBM as a routine component of inpatient withdrawal treatment.

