### Interventions

The CBM training is a modified training version of the assessment AAT. Participants are instructed to respond to digitally presented images with a push or pull motion, using a joystick, based on the orientation of the framing of the picture (pushing landscapes; pulling portraits). The training task has been programmed to scale up and down the images in response to pull and push movements, respectively, to simulate the picture expanding towards the participant when ‘pulled’ and receding into the distance when ‘pushed’. As a component of each training session, participants complete a brief practice round involving eight empty frames, to familiarise them with the task requirements. Following the eight practice trials, participants are exposed to presentations of 40 images of alcoholic and 40 images of non-alcoholic beverages, in a random order. Each alcoholic and non-alcoholic beverage is presented three times, for a total of 240 image presentations. Landscape-oriented frames contain alcoholic images in 95% of presentations, implicitly training participants to respond to alcohol with an avoidance movement. The remaining 5% of landscape-oriented presentations contain images of non-alcoholic beverages. Likewise, portrait-oriented images contain non-alcoholic images in 95% of presentations, and alcohol-related images the remaining 5% of the time. During each presentation, the image scales until the joystick reaches its maximal distance. If the response is correct, the next trial then commences after a 500 millisecond inter-stimulus interval (ISI). If the response is incorrect, a large red ‘X’ flashes on the screen and the trial is repeated until the correct response is performed.

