### Outcome measures

The primary outcome of interest to this study is the difference between treatment arms in proportion of participants reporting abstinence from alcohol 2 weeks after discharge, measured with the TLFB. Secondary outcomes of interest are abstinence at the subsequent follow-ups (measured with the TLFB), the difference between treatment arms in healthcare costs incurred due to acute/emergency healthcare treatment and readmission to AOD withdrawal treatment during the follow-up period (service use measured with the LDUH, with costs of treatment episodes to be estimated with the assistance of a health economist), and differences in cue-evoked desire for images of alcohol after the final session of CBM training. Secondary analysis will also examine the degree to which baseline approach bias towards alcohol moderates the effectiveness of CBM training on the primary outcome. Additional exploratory analyses are planned to investigate (i) moderating effects of pre-admission history of withdrawal treatment, severity of alcohol dependence and cravings, and impulsivity on the primary and secondary outcomes; (ii) whether alcohol cravings (as measured by the ACQ-SF-R) are affected by CBM; and (iii) whether CBM affects time to relapse.

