### Other secondary outcomes

Other secondary outcomes that are binary will be analysed in the same way as the key secondary outcome measure, including supplementary analyses (as above). The moderating effect of baseline approach bias score on abstinence/relapse in the 2 weeks post discharge (i.e. the primary outcome) will be investigated by logistic regression models that include baseline scores as covariates in the model and tests of the significance of the two-way interaction of treatment arm with the covariate will be conducted. A similar approach will be used to test for a moderating effect of impulsivity, as measured by the BART.

Continuous-scale outcome measures, and ordinal scale outcomes that have five or more ordered categories, will be analysed using mixed models, and the restricted maximum likelihood (REML) method, with random effects for participants and assessments within participant, and fixed effects for treatment arm, time and baseline covariates. Diagnostic plots of residuals will be examined and, if required, analyses will be conducted using a variance-stabilising transformation such as the log transformation or the empirical logit transformation.

To determine the economic feasibility of CBM, in terms of savings to the treatment system (evidenced by fewer repeat inpatient withdrawal treatment episodes and episodes of acute health service use at the 12-month follow-up), we will compare net spending (cost of CBM intervention plus cost of further withdrawal/acute health service use for each participant) in the CBM group to net spending (cost of further withdrawal/acute health service use) in the control group. The statistical significance of the difference between the groups will be assessed with a *t* test and a variance-stabilising transformation, such as the logarithm, will likely be required.

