For cue-evoked wanting, outcomes will be assessed with a mixed model (repeated measures) analysis assessing within-subjects variables of ‘time’ (pre-training/post-training), ‘picture-type’ (alcohol/non-alcohol), and ‘novelty’ (used in training/not used in training), with the between-subjects conditions of ‘group’ (CBM/Control). Particular attention will be paid to comparisons of time, picture-type, and group within each level of novelty. The number and proportion of participants who require cessation of one or more training sessions due to distress or fear of relapse, and who require permanent cessation of training for these reasons, will be reported as a measure of the safety of the CBM training. Statistical analyses will be conducted using the most appropriate procedures in GenStat, 19th Edition (VSN International, Hemel Hempstead, UK), SAS Version 9.4 (SAS Institute, Inc., Cary, NC, USA) and R (R Foundation for Statistical Computing, Vienna, Austria), or later versions of the software as they become available.

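### Cue-evoked wanting: the pre-randomisation rating is modelled as a response, which is valid but gives a less precise arm contrast than baseline adjustment

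*Protocol article*

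**What the plan says.** The Aims section of the protocol article asks whether participants given CBM "will demonstrate a reduction in self-reported cue-evoked desire (wanting) for alcohol compared to those who undergo sham training". Outcome measures lists, as a secondary outcome, "differences in cue-evoked desire for images of alcohol after the final session of CBM training". Both concern alcohol.

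The analysis is at the end of the statistical methods, under Other secondary outcomes: "For cue-evoked wanting, outcomes will be assessed with a mixed model (repeated measures) analysis". The factors are "within-subjects variables of ‘time’ (pre-training/post-training") together with "picture-type’ (alcohol/non-alcohol), and ‘novelty’ (used in training/not used in training"), and group is the only between-subject term. The text then says: "Particular attention will be paid to comparisons of time, picture-type, and group within each level of novelty". No single contrast is named as the main one, and the word interaction does not appear.

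Three other places bear on this:

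- The general rule for continuous outcomes, earlier in the same section, has "fixed effects for treatment arm, time and baseline covariates". The wanting model is set out separately and mentions no baseline covariate.
- Procedure places randomisation after the pre-training measures and repeats the ratings once, after the final session.
- Interventions states that in CBM "portrait-oriented images contain non-alcoholic images in 95% of presentations", portrait being the pulled orientation. In sham training each orientation is split equally between picture types and the movements are lateral.

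**The concern.** The pre-training rating is measured before allocation, so its expected mean is the same in both arms. A model that makes this rating a response and lets each arm have its own pre-training mean estimates a difference that randomisation has already set to zero in expectation. The arm effect is then the difference between arms in change, and it carries the full sampling noise of the baseline difference. Adjusting for the baseline, or constraining its mean to be equal across arms, estimates the same effect with smaller variance from the same data.

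The second issue is which contrast is read as the answer. The outcome is wanting for alcohol pictures, while the sentence on emphasis puts picture type beside time and group. A group-by-time-by-picture-type term measures the change for alcohol pictures in excess of the change for non-alcohol pictures. The arms are trained differently on non-alcohol pictures, so that excess is not the same quantity as the effect on alcohol wanting.

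At stake are the precision and clarity of one secondary outcome, which the Discussion relies on for insight into mechanism. The primary outcome is not affected.

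**Working it through.** **Inputs.** The documents give no standard deviation, correlation, effect size or power for wanting. The pre-post correlation r, the correlation r_c between the alcohol and non-alcohol changes, and the effect size are therefore assumptions, shown over ranges. The only sample-size figure is for the primary outcome. The two-proportion calculation (65% vs 45%, two-sided 0.05, 90% power, pooled variance) reproduces 128 per arm, 256 in total. It does not bear on wanting; 128 per arm is borrowed below only as an illustrative size.

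**Step 1: precision of the alcohol-picture contrast.** Take equal pre and post variance σ² and n per arm, and express the variance of the arm contrast in units of 2σ²/n.

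- Group-by-time with free baseline means: 1 + 1 − 2r = 2(1 − r).
- Baseline-adjusted, or common baseline mean: 1 − r².
- Ratio, adjusted to change score: (1 − r²) / [2(1 − r)] = (1 + r)/2.

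The power column sets the effect so that the adjusted contrast has 90% power at 128 per arm.

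| r (assumed) | Change score 2(1−r) | Adjusted 1−r² | Ratio (1+r)/2 | Inverse | Power of group-by-time |
|---|---|---|---|---|---|
| 0.3 | 1.40 | 0.91 | 0.65 | 1.54 | 74% |
| 0.5 | 1.00 | 0.75 | 0.75 | 1.33 | 80% |
| 0.7 | 0.60 | 0.51 | 0.85 | 1.18 | 85% |
| 0.9 | 0.20 | 0.19 | 0.95 | 1.05 | 88% |

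The inverse column is the factor by which a change-score analysis would need more participants to match the adjusted one.

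**Step 2: simulation check.** 4,000 runs, 128 per arm, r = 0.6, true alcohol effect −0.35 SD. The change-score contrast had mean −0.350 and standard error 0.112; the baseline-adjusted contrast had mean −0.351 and standard error 0.101. Both recover the true effect. The variance ratio is (0.101/0.112)² = 0.81, against (1 + 0.6)/2 = 0.80 from the formula.

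**Step 3: what the three-way term measures.** It is the arm difference in [alcohol change − non-alcohol change].

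- If CBM moves alcohol wanting by 0 and non-alcohol wanting by +5 points relative to sham, the term is 0 − 5 = −5 points, with no effect on alcohol wanting.
- If both fall equally, the term is zero. In the simulation its mean was 0.000 although alcohol wanting fell by 0.35 SD.

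In the same units its variance is 4(1 − r)(1 − r_c). At r = 0.5 this is 2.0, 1.4, 1.0 and 0.6 for r_c = 0, 0.3, 0.5 and 0.7, against 1.0 for the alcohol-only change score and 0.75 for the adjusted contrast. If non-alcohol wanting does not respond to training, power at the effect used in step 1 is 51%, 66%, 80% and 95%. The three-way term is thus less precise than the alcohol-only change contrast only when r_c is below 0.5. The reason not to let it decide is what it estimates, not a general lack of power.

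**The case against.** The strongest reply is that the plan is a valid analysis and that nothing in it rules out the better one. The baseline is used, the change contrast is unbiased under randomisation, and it answers an objective phrased as a reduction. A mixed model with a common baseline mean is still a repeated-measures model with time as a factor, so it fits the stated wording, and the general rule for continuous outcomes does mention baseline covariates. The planned model can also keep participants with one rating missing. That matters because the Discussion accepts that secondary measures are sometimes dropped for fatigue, distress or lack of time; a plain covariate-adjusted analysis of the post-training rating would lose those without it. Finally, the analysis plan, which is not shown, may settle the contrast.

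Much of this stands. It favours the constrained-baseline form over plain covariate adjustment. It does not remove the gain, because the wanting model is written out separately with neither a baseline covariate nor a common baseline mean, and would ordinarily be fitted with free means.

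A reader might also infer that the plan tests only the three-way interaction and so fails to isolate alcohol wanting. The text does not support that. It names no deciding test, and the alcohol-only group-by-time contrast, overall and by novelty, can be estimated from the model described. Non-alcohol pictures are a defensible check that any change is specific to alcohol rather than a general shift in wanting. Nor does the protocol say that non-alcohol wanting will rise; the 5-point example is hypothetical.

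**Conclusion.** The point holds as a matter of precision and specification in one secondary outcome. It is not an error that biases the result. With free baseline means, the planned arm contrast for alcohol pictures has variance 1.54, 1.33, 1.18 or 1.05 times that of the baseline-adjusted contrast at r = 0.3, 0.5, 0.7 or 0.9. These figures assume equal pre and post variances and correlations that the documents do not supply; at high r the loss is small. To say that the plan wastes the baseline would go too far, since the rating is used, only less efficiently than it could be.

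On targeting, the conclusion is conditional. If the group-by-time-by-picture-type term were taken as the deciding test, it would answer a different question from the stated objective and outcome, because CBM also trains responses to non-alcohol pictures. The protocol neither commits to that use nor excludes it.

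**What to change.** Keep the repeated-measures mixed model and specify, before the wanting data are analysed:

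- Constrain pre-training means to be equal across arms. Adjusting for the participant's pre-training alcohol-picture rating is an alternative, but the constrained form is preferred because it keeps participants with either rating missing.
- Include site, since allocation is stratified by site.
- Make the post-training arm difference in wanting for alcohol pictures the main contrast.
- Report trained and novel alcohol pictures as planned contrasts, which serves the stated interest in generalisation.
- Report non-alcohol pictures and the three-way term as supportive checks of specificity.

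The cost is wording in the analysis plan and a little more analysis work. All the ratings are already part of the schedule.

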#### Alcohol cravings

Alcohol cravings are assessed using the Alcohol Craving Questionnaire – Short Form – Revised (ACQ-SF-R) [41]. In addition, to monitor participant safety (related to the potential for exposure to alcohol-related imagery to trigger cravings), participants self-rate the intensity of their craving for alcohol immediately before and following each CBM training session, using a single-item visual analogue scale (anchored at the left and right ends with ‘not at all’ and ‘extreme’, respectively). In addition, participants view 20 computerised images (10 of alcoholic beverages and 10 of non-alcoholic beverages) and rate the magnitude of their ‘wanting’ of the pictured beverages by marking a point along an accompanying line with end caps either side indicating ‘I do not want this at all’ to ‘I really want this’. Scores range from 0 to 100, based on the position of the mark (i.e. a mark on the extreme left of the line results in a score of 0 being recorded, while a mark on the extreme right of the line results in a score of 100 being recorded). Within each of the two beverage categories (alcoholic; non-alcoholic), five of the 10 images are identical to images used in the training task (see below) and the other five are novel images not used in other study tasks. This is to allow assessment, following training, of generalisation of reduced cue-evoked wanting from images used in training to other alcohol-related images.

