Instability in residential status, relationships and employment is common among this population, and this makes follow-up assessment particularly challenging. In our pilot study of CBM training [37], 86% of the sample completed the 2-week follow-up. Based on previous research [44], we anticipate retention of approximately 70% of participants at the 12-month follow-up. To support these targets, during the course of recruitment and consent, participants are asked to provide several means of contact, such as home and mobile phone numbers, email, postal addresses, and multiple secondary contacts, such as family members, friends, or significant others. Researchers conducting follow-ups are available to contact participants at any time of their choosing, and participants are reimbursed AUD 10 for completing each of the follow-ups. At each follow-up, participants are reminded of any upcoming follow-ups to minimise attrition.

Due to the nature of the training task (exposure to images of alcohol), it is expected that participation will trigger cravings or distress in some participants. To monitor this, and minimise adverse consequences for the participants, participants rate their craving for alcohol immediately prior to and following administration of each training session. If a participant reports strong cravings following a session, researchers offer information on a mindfulness-based technique developed to aid patients in recovery manage instances of strong cravings. In extreme cases, or at the request of participants, researchers immediately seek the assistance of clinical staff to intervene with appropriate clinical management. Training sessions are immediately discontinued in the event that a participant expresses distress or intense craving during a session. If this occurs, with the participant’s permission, assistance is sought from the clinical staff, and their continued participation is subject to review. Any reports of severe cravings or distress are recorded to monitor the safety of this intervention, and participants are reminded that they may withdraw their participation at any time without adverse consequences. At the end of phone follow-ups, participants are offered the contact details of a free 24-h telephone and web-based alcohol and drug counselling and referral service in case the follow-up questionnaires have triggered distress or cravings.

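### The safety count lists distress and fear of relapse, but sessions are stopped for distress or intense craving, so stops for craving alone fall outside the count as written

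*Protocol article*

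**What the plan says.** Three places in the protocol article bear on this.

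- **Other secondary outcomes, final paragraph (the reported measure).** The article will give the number and proportion of participants who have to stop at least one session because of "distress or fear of relapse, and who require permanent cessation of training for these reasons, will be reported as a measure of the safety".
- **Discussion, paragraph on the effects of exposure to alcohol images (the operating rule).** The article states that "it is expected that participation will trigger cravings or distress in some participants". It then says: "Training sessions are immediately discontinued in the event that a participant expresses distress or intense craving during a session". After such a stop, the participant's continued participation is reviewed. It adds: "Any reports of severe cravings or distress are recorded to monitor the safety of this intervention".
- **Measures, Alcohol cravings (the monitoring tool).** Each participant marks a single-item visual analogue scale for craving, once before and once after every session. The stated purpose of these ratings is "to monitor participant safety (related to the potential for exposure to alcohol-related imagery to trigger cravings".

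**The concern.** A safety measure based on stopped sessions should count the events that stop sessions. Here the rule for stopping and the rule for counting name different reasons. Intense craving stops a session but is not a counted reason. Fear of relapse is a counted reason but does not appear in the stopping rule.

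The reason left out is not a marginal one. Craving provoked by alcohol images in people undergoing withdrawal is one of the two harms that the article says it expects, and it is the stated purpose of the ratings taken around each session. If the count is produced exactly as worded, the published proportion could understate how often training had to be stopped for that harm, and a reader would take the lower figure as evidence of tolerability.

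**Working it through.** No arithmetic in the article bears on this point, so the check sets the texts side by side.

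| Reason | Stops a session (Discussion) | Recorded for safety (Discussion) | Counted in the safety measure (Other secondary outcomes) |
|---|---|---|---|
| Distress | Yes | Yes | Yes |
| Intense or severe craving | Yes | Yes | Not named |
| Fear of relapse | Not named | Not named | Yes |

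**Step 1: is craving counted under another name?** The measure gives two reasons and then refers back to those same two for permanent cessation. Neither is craving. The Discussion treats craving and distress as alternatives joined by *or*, both in the stopping rule and in the recording rule, so within this document distress does not plainly include craving.

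**Step 2: who would be missed?** The measure counts participants, not sessions. A participant with one stop for distress and another for craving is still counted once. The participants lost are those whose every stop was recorded as craving only. The same holds for permanent cessation, where the loss is those whose permanent stop was recorded as craving only.

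**Step 3: how large is the loss?** Let T be the number of participants in an arm with at least one stop for any of the three reasons, and let f be the fraction of them whose stops were all recorded as craving only. Then

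reported count = T × (1 − f), and the relative shortfall is f.

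The article gives neither T nor f. If staff always record a craving stop as distress or fear of relapse, f = 0 and nothing is lost. If every stop is recorded as craving only, f = 1 and nothing is counted. The documents do not narrow this range, so the direction of the error is known (downward or none) but its size is not.

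**Step 4: is this a detail left to the SAP?** The article does not leave the counted reasons open. It states them, and the statement conflicts with the Discussion. The article's pointer to the SAP closes the section on the key secondary outcome and moderation, not the safety text. An SAP that copied the safety sentence would carry the mismatch forward.

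**The case against.** The best case against the point is that the labels overlap in practice. Someone who must stop because of intense craving may well be distressed, afraid of relapsing, or both, and the researcher may record it so. Nothing in the article says that the labels are mutually exclusive. This stands, and it is why no size can be put on the undercount. It does not remove the point: the count would then depend on which word a researcher happened to write down.

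A reader might also infer more than the documents support:

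- **That the safety report omits the harm the protocol names.** It does not. Distress, the other expected harm, is counted, and the article calls the count *a* measure of safety, not the only one.
- **That the per-session craving ratings are never analysed.** This cannot be shown. The SAP is not at hand and a table of a monitoring scale is commonly left to it. The general mixed-model rule for continuous outcomes could be applied to the scale, although the scale is not named as an outcome. The ratings also have an immediate use: the Discussion describes help offered to participants who report strong cravings after a session.
- **That the trial ignores craving.** It does not. An exploratory analysis of the craving questionnaire and a model of cue-evoked wanting are both planned.
- **That the arms will not be compared on safety.** The article is silent on layout, and silence is not pooling.
- **That the loss can be quantified, for example as half of all stops.** No figure in the article supports any such share. Nor can the precision of a craving-score comparison be stated, because the article gives that scale verbal end-points but no numerical range; the 0 to 100 range belongs to the picture-wanting ratings.

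**Conclusion.** The mismatch is real and lies in stated text: of the reasons named in the two sections, only distress is common to both. Taken as written, participants whose training stopped for intense craving alone are left out of the safety count, so the reported proportions could be too low for a harm the article expects. The relative shortfall is the unknown fraction f above, anywhere from none upwards. The conclusion rests on a literal reading of the safety sentence and on at least some craving stops not being recorded under another label. The primary and key secondary analyses are unaffected. The absence of a named summary for the session craving ratings is a supporting remark only.

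**What to change.** Reconcile the safety sentence in Other secondary outcomes with the stopping rule in the Discussion. The safety report should give, by arm and by recorded reason, the number of sessions discontinued and the number and proportion of participants with one or more discontinued sessions, and with permanent cessation, for distress, intense craving or fear of relapse. More than one reason should be allowed per stop, with a total over all three, so that the total does not depend on the label chosen. This concerns counting only and leaves the clinical stopping rule untouched. Both arms see the same alcohol images, so the counts within each arm matter as well as the difference between arms.

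Optionally, add a summary by arm of the craving ratings before and after each session, if the SAP does not already provide one.

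The cost is a sentence or two and a few table rows. Reports of severe cravings or distress are already recorded. The one practical check is that the study records show the reason for each stopped session clearly enough to classify it. The wording should be settled before the safety data are tabulated by arm.
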